**Sample size/power calculation**

The main analysis is on opiate substation treatment (OST) in primary care and risk of death and in particular the comparison of methadone and buprenorphine*.

There will be at least 20,000 OST patients (extracted from CPRD GOLD patients) from 1998 to 2014 linked to NHS central registry and ONS mortality data, that will generate 67,000 person years (pys) follow-up (~32,000 on treatment and ~35,000 off) if censored 12 months after last OST. There will be over 700 deaths of which ~500 will be due to overdose. This will be the largest study in the UK with precise data on OST treatment exposure (including ~ 12000 pys on buprenorphine and 30,000pys on methadone). In addition, there will be approximately 10,000 and 12,000 person years in treatments lasting less than 1 month or greater than 12 months, and 3000 and 1200 person years follow-up in the first 4 weeks treatment on or immediately after methadone or buprenorphine treatment respectively.

Thus, there is sufficient power (> 90%) to determine whether:-

1. there is at least a halving of the risk of death during treatment on burpenorphine compared to methadone (i.e. 0.35% vs. 0.69% respectively) – which requires a sample of at least 922 in each group compared to 12,000 and 20,000 on buprenorophine and methadone
2. and sufficient power (80%) to test if the risk of death is at least a 1/3 lower on buprenorphine at (0.006%) compared to methadone (0.016%) in the first 4 weeks of treatment (1200 and 3000 person years respectively) – as indicated by unpublished analyses by Degenhardt on Australian mortality cohort(9).

In addition, there is sufficient power to corroborate that the risk of fatal overdose out of treatment at 0.8% is twice as high as the risk during treatment – which will require sample of at least 788 in and out of treatment compared to our sample of over 30,000 person years in each group; and that the risk of death in the 4 weeks after treatment at about 4.6% is 1/3 lower (3.0%) for people treated for short duration of treatment (< 1 month) compared to those treated for 12 months or longer – which will require sample of at least 3123 in each group compared to over 3500 and 3850 person years among those exposed to short or prolonged treatment respectively;

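### The person-years offered for comparing death in the 4 weeks after short versus long treatment do not fit the protocol's own totals, so the claim of sufficient power is not supported

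*Protocol*

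**What the plan says.** The claim is the last one on the primary care cohort in the Protocol, section Sample size/power calculation. It says power suffices to show that "the risk of death in the 4 weeks after treatment at about 4.6% is 1/3 lower (3.0%) for people treated for short duration", the comparator being treatment of 12 months or longer. The long arm therefore carries 4.6% and the short arm 3.0%. Need and supply are set side by side: "sample of at least 3123 in each group compared to over 3500 and 3850 person years among those exposed to short or prolonged treatment". No power, alpha or sidedness is given for this claim.

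The same section supplies the totals to check it against:

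- overall follow-up: "67,000 person years (pys) follow-up (~32,000 on treatment and ~35,000 off";
- by treatment duration: about 10,000 and "12,000 person years in treatments lasting less than 1 month or greater than 12 months";
- by 4-week window: "3000 and 1200 person years follow-up in the first 4 weeks treatment on or immediately after methadone or buprenorphine treatment".

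The section Exposures, outcomes and covariates treats the first 4 weeks after treatment as a period of its own, separate from the rest of the time out of treatment.

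**The concern.** Four weeks is one thirteenth of a year, so thousands of person-years in such windows need tens of thousands of cessations. After long treatment, each of those cessations also needs at least a year on treatment first. The section's own on-treatment total looks too small for that.

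Treatment duration heads the modifiable factors in the over-arching hypotheses, and the modelling part of the analysis plan will project the effect of changing it. If the claim stands, a null short-versus-long result could be read as coming from a test with about 90% power when the exposure to support that reading is not there.

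**Working it through.** **Inputs.** All are from Sample size/power calculation: 4.6% (long) and 3.0% (short); 3,123 needed per group; 3,500 (short) and 3,850 (long) person-years available; 32,000 person-years on treatment; 10,000 and 12,000 person-years in treatments under 1 month and over 12 months; 3,000 + 1,200 = 4,200 person-years in 4-week windows; over 700 deaths; at least 20,000 patients. Alpha is assumed to be 0.05, two-sided.

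**1. The required size reproduces.** For two proportions with pooled variance under the null, z = 1.960 and 1.282:

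n = [1.960·√(2·0.038·0.962) + 1.282·√(0.046·0.954 + 0.030·0.970)]² / 0.016² = 2,999.

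With continuity correction, n/4·[1 + √(1 + 4/(n·0.016))]² = 3,122.5, which rounds up to 3,123. The stated need therefore corresponds to 90% power, and the problem lies in the supply.

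**2. The long arm.** One cessation gives at most 4/52 = 1/13 year.

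- 3,850 × 13 = 50,050 cessations of treatments lasting at least 12 months, hence at least 50,050 person-years on treatment. The section gives 12,000 in such treatments and 32,000 in total.
- Ceiling from 12,000: 12,000/13 = 923 person-years. The stated figure is 3,850/923 = 4.2 times that.
- Ceiling if all 32,000 were in treatments of exactly 12 months: 32,000/13 = 2,462, still below 3,123.

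**3. The pair.** 3,500 + 3,850 = 7,350, against 4,200 stated for 4-week windows over both drugs and all durations.

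**4. The short arm alone.** 3,500 × 13 = 45,500 cessations. At up to one month each, these need at most 45,500/12 = 3,792 person-years on treatment, which fits within 10,000. So 3,500 by itself is not impossible.

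**5. Power with the long arm at 923.** Power = Φ(ln(4.6/3.0)/√(1/d₁ + 1/d₂) − 1.96), where ln(4.6/3.0) = 0.4274 and d = person-years × rate, reading 4.6 and 3.0 as deaths per 100 person-years:

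| Long, short (person-years) | Expected deaths | Power |
|---|---|---|
| 3,850, 3,500 (as stated) | 177, 105 | 93% |
| 923, 923 | 42.5, 27.7 | 42% |
| 923, 3,500 | 42.5, 105 | 65% |
| 923, 9,231 | 42.5, 277 | 74% |

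The 9,231 takes the 10,000 person-years as 120,000 treatments of one full month: 120,000/13 = 9,231. That is already six short treatments per patient and more than twice the 4,200. Treatments shorter than a month would give more windows on paper, but this does not change the result. With an unlimited short arm the formula tends to Φ(0.4274·√42.5 − 1.96) = Φ(0.83), which is just under 80%.

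**6. Other readings of the sentence.**

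- *All post-treatment time.* The figures equal 10% and 11% of the 35,000 off-treatment person-years, which hints at this. They would then be the wrong denominator for a 4-week comparison.
- *True 4-week risks with the stated person-years.* 50,050 × 4.6% + 45,500 × 3.0% = about 3,670 deaths, against over 700 in the whole study.
- *Cessations mislabelled as person-years, with true 4-week risks.* Power would be about 95%. But 4.6% × 13 is about 60 deaths per 100 person-years, some 87 times the 0.69% given for methadone treatment, where the Background speaks of more than 8 times. Read as an annual rate, 4.6/0.69 = 6.7 times, which is of the Background's order.

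**The case against.** The sentence never says that the 3,500 and 3,850 person-years fall inside the 4-week window. That stands, and it is why the point is put as two alternatives: impossible for the long arm if they do, and the wrong denominator if they do not. Neither supports the power claim.

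The section's inputs disagree with one another. It lists 12,000 and 30,000 person-years on the two drugs, which sum to 42,000, against 32,000 on treatment. The 10,000 person-years in treatments under a month imply at least 120,000 treatments. This is a fair warning against treating any single replacement power figure as the true one. It does not restore 3,850: even 42,000/13 = 3,231 falls short of it.

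A reader might infer more than the documents support:

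- *That neither figure could exist in this cohort.* Step 4 shows that 3,500 alone could.
- *That the 4,200 person-years are a firm cap on post-treatment time, or that half of them are post-treatment.* The wording covers time on treatment or just after it, and the second listed power claim uses all 3,000 and 1,200 for the first 4 weeks of treatment. Without that cap, and with all 32,000 on-treatment person-years put into 12-month treatments, 2,462 against 3,500 would give 88% power. That case contradicts the section's own 12,000, so it does not rescue the claim, but it shows that the power ceiling depends on the 12,000.

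Finally, the contrast is secondary. Methadone versus buprenorphine is the main comparison, the Limitations section promises caution over single tests, and the December 2015 amendment admits underpowered analyses. All of this limits the consequence. The amendment concerns the number of deaths and their linkage to cause, and it leaves this sentence uncorrected.

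**Conclusion.** The claim is wrong as written. The long-arm 3,850 is at least 4.2 times what 12,000 person-years in treatments over 12 months can yield in 4-week windows, and the pair conflicts with the stated 4,200. On the protocol's present figures, power for 3.0 versus 4.6 per 100 person-years is about 42% to 74%, and under 80% whatever the size of the short arm, against the 90% that 3,123 per group implies.

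This rests on three assumptions: a two-sided 5% test, the two percentages read as annual rates, and the 12,000 read as on-treatment time. The required 3,123 is not in question. Nor does this point show that the main methadone–buprenorphine comparison lacks power, or that the duration contrast must be relabelled as estimation only. It concerns one stated design property of a secondary contrast.

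**What to change.** In Sample size/power calculation:

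1. Recount the person-years in weeks 1–4 after cessation from the expected number of cessations, grouped by completed duration of the episode that ended.
2. Reconcile the recount with the 12,000, 32,000 and 4,200 totals in the same section, and say what each total covers.
3. Replace 3,500 and 3,850 with the recounted figures.
4. Remove the statement of sufficient power for this contrast and give the power or detectable rate ratio that the recount supports, with alpha and sidedness. On the present figures that is no more than about 74%, taking short treatments at a full month each.

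The cost is a recount from planning data and a rewritten sentence. No further patients or analyses are needed. The downside is that a stated figure becomes less favourable.

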**Study population**

The study population comprise all patients aged 16-64 who have been prescribed methadone or buprenorphine as opiate substitution treatment (OST) in CPRD practices from 1997 to 2014, including a sub-set of patients eligible for ONS linkage. opiate dependent people treated with opiate substitution drugs on CPRD. The table shows the initial set of criteria. Prescription dose and diagnoses will be checked to confirm that prescription for OST and to exclude any patients prescribed for pain/analgesia.

| **prodcode** | **Productname** |
| --- | --- |
| 3064 | Buprenorphine 400microgram sublingual tablets sugar free |
| 3522 | Temgesic 200microgram sublingual tablets (RB Pharmaceuticals Ltd) |
| 6056 | Buprenorphine 8mg sublingual tablets sugar free |
| 6210 | Subutex 8mg sublingual tablets (RB Pharmaceuticals Ltd) |
| 6547 | Buprenorphine 2mg sublingual tablets sugar free |
| 7457 | Temgesic 0.3mg/ml Injection (Reckitt Benckiser Healthcare (UK) Ltd) |
| 8017 | Temgesic 400microgram sublingual tablets (RB Pharmaceuticals Ltd) |
| 10077 | Subutex 2mg sublingual tablets (RB Pharmaceuticals Ltd) |
| 13031 | Subutex 0.4mg sublingual tablets (RB Pharmaceuticals Ltd) |
| 35269 | Temgesic 300micrograms/1ml solution for injection ampoules (RB Pharmaceuticals Ltd) |
| 40211 | Buprenorphine 2mg sublingual tablets sugar free (Teva UK Ltd) |
| 40212 | Buprenorphine 8mg sublingual tablets sugar free (Teva UK Ltd) |
| 40473 | Buprenorphine 300micrograms/1ml solution for injection ampoules |
| 35169 | Suboxone 8mg/2mg sublingual tablets (RB Pharmaceuticals Ltd) |
| 35170 | Suboxone 2mg/500microgram sublingual tablets (RB Pharmaceuticals Ltd) |
| 35681 | Buprenorphine 2mg / Naloxone 500microgram sublingual tablets sugar free |
| 35682 | Buprenorphine 8mg / Naloxone 2mg sublingual tablets sugar free |
| 38311 | Naloxone hc 2mg + 8mg Tablet |
| 42074 | Naloxone hc 500micrograms + 2mg Tablet |
| 2952 | Methadone 1mg/ml oral solution |
| 5211 | Methadone 2mg/5ml linctus |
| 5322 | Physeptone 5mg tablets (Martindale Pharmaceuticals Ltd) |
| 6441 | Methadone 5mg tablets |
| 9728 | Methadone 1mg/ml oral solution sugar free |
| 11722 | Methadone 10mg/ml oral solution sugar free |
| 14086 | Methadone 10mg/ml Injection |
| 17671 | Methadone 50mg/1ml solution for injection ampoules |
| 17896 | Physeptone 10mg/ml Injection (Martindale Pharmaceuticals Ltd) |
| 21562 | Physeptone 1mg/ml mixture sugar free (Martindale Pharmaceuticals Ltd) |
| 23158 | Methadone 20mg/ml oral solution sugar free |
| 24343 | Methadose 10mg/ml oral solution concentrate (Rosemont Pharmaceuticals Ltd) |
| 24361 | Methadose 20mg/ml oral solution concentrate (Rosemont Pharmaceuticals Ltd) |
| 24440 | Methodex 1mg/ml Mixture (Link Pharmaceuticals Ltd) |
| 24584 | Methadone 50mg/2ml solution for injection ampoules |
| 26277 | Physeptone 1mg/ml mixture (Martindale Pharmaceuticals Ltd) |
| 28328 | Metharose 1mg/ml oral solution sugar free (Rosemont Pharmaceuticals Ltd) |
| 29304 | Physeptone 10mg/1ml solution for injection ampoules (Martindale Pharmaceuticals Ltd) |
| 29769 | Methadone 2mg/5ml Oral solution (Martindale Pharmaceuticals Ltd) |
| 29911 | Methadone 2mg/5ml linctus (Thornton & Ross Ltd) |
| 30531 | Methadone 1mg/ml oral solution sugar free (Rosemont Pharmaceuticals Ltd) |
| 32237 | Methex 1mg/ml Mixture (Generics (UK) Ltd) |
| 33068 | Methadone 10mg/1ml solution for injection ampoules |
| 33475 | Methadone 35mg/ml Injection |
| 33832 | Methadone 1mg/ml oral solution (Martindale Pharmaceuticals Ltd) |
| 35506 | Methadone 20mg/2ml solution for injection ampoules |
| 36436 | Methadone 50mg/5ml solution for injection ampoules |
| 36994 | Methadone 5mg/ml oral solution |
| 37507 | Physeptone 50mg/1ml solution for injection ampoules (Martindale Pharmaceuticals Ltd) |
| 37518 | Methadone 35mg/3.5ml solution for injection ampoules |
| 39437 | Eptadone 1mg/ml oral solution (Dee Pharmaceuticals Ltd) |
| 41608 | Methadone 1mg/ml oral solution (Rosemont Pharmaceuticals Ltd) |
| 41720 | Methadone 1mg/ml Mixture (Macarthy Medical Ltd) |
| 43260 | Methadone Oral solution |
| 43766 | Eptadone 5mg/ml oral solution (Dee Pharmaceuticals Ltd) |

**Selection of comparison group(s) or controls**

Patients are their own comparison group/ controls – as we will be comparing risk of mortality at different periods during and after opiate substitution treatment.

**Exposures, outcomes and covariates**

*Exposure:-* OST includes methadone and buprenorphine and occasionally dihydrocodeine(6, 11). Intervention exposure is defined by prescribing data collected by primary care practices contributing information through their electronic health record systems to the Clinical Practice Research Datalink (CPRD). This will include information on all prescriptions in primary care plus other information on diagnoses and attendances at primary care and hospital. We will extract information on patients on the basis that they have a drug misuse diagnosis and have been prescribed methadone or buprenorphine. Some patients also may have been prescribed dihydrocodeine as OST – and so we will include these treatment episodes as well. The information provided by CPRD will allow us to establish when OST started, changes in dose or type of OST, and when OST ceased. For each treatment period we will classify different periods “on”/during or “off”/after OST or other drug treatment e.g. 1st 2 weeks of treatment, rest of time on treatment (baseline treatment period), 1st 4 weeks after treatment, and rest of time out of treatment (censored at 12 months after last prescription); as well as measure average OST duration and classify treatment duration (≤ 1 month, 2-6 months, 7-12 months, 12+months).

*Main outcome:* All and cause specific death (in particular drug poisoning/overdose) during drug treatment or follow-up period up to one year after date of last opiate substitution treatment (OST) prescription/treatment admission. Standard codes for drug related poisonings deaths will be used to define overdose deaths (23): ICD-10 codes: F11-16; F18-19; X40-44; X60-64; X85; Y10-14; as well as in terms of general and specific drugs mentioned on the death certificate (any opiate, heroin and Morphine, Methadone, buprenorphine, dihydrocodeine, other opiods, cocaine, all amphetamines and MDMA, GHB, GBL, all benzodiazepines, barbiturates, all antidepressants, paracetamol and other over the counter medicines). We will categorise deaths as “avoidable” and “preventable” based on ONS definitions (<http://www.ons.gov.uk/ons/publications/re-reference-tables.html?edition=tcm%3A77-262418>). Other specific causes that will be investigated include suicide and other injury (non drug related poisoning), infectious diseases, cirrhosis and liver disease. All cause mortality will be expressed as a rate and as a Standardised Mortality Ratio (SMR) compared to standard age and sex death rates for England and Wales. Cause specific mortality will be expressed as rates – and SMRs also will be calculated for non-drug related poisonings. Follow-up of patients extracted from primary care database (Clinical Practice Research Datalink, CRPD) will be from date of first OST prescription within risk period beginning 1990 to end 2011. A patient’s follow up will cease either one year after the expiry of their last prescription for OST or the date of death or on the date of transfer out from the general practice or risk study period end (which ever date occurs first). [Follow-up of patients extracted from Drug Data Warehouse (DDW) will be from 2005 to 2009 the period for which National Drug Treatment records are linked to the mortality register.] We are censoring follow-up twelve months after last prescription or specialist drug treatment date in order to reduce potential bias.

Secondary outcomes concern the practice and delivery of OST including:- annual number of people in OST; modality/specific OST drug; duration of OST; dose; evidence of reaching optimal dosage, tapering OST dose towards planned discharge, and supervised consumption; and co-prescription of benzodiazepines.

*Covariates/confounders:-* Additional exposures (benzodiazepines, treatment performance/quality) and confounders (age, gender, co-morbidity as defined by Charlson Index(24), alcohol and mental health problems, treatment episode number, calendar year, other prescription drugs) all of which have been shown to influence mortality risk(11) (9). Supervised prescription will need to be coded through analysis of free-text – which will be piloted and developed with CPRD. A sample of records with full free text will be used to identify key words and search terms that can define the variable “evidence of supervised consumption”. The key words and search terms can then be used across the whole database to record the covariate.

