| 1. If you are seeking access to data held under the CPRD Data Linkage Scheme, please provide the following information:   The number of linked datasets requested: CPRD with ONS mortality register  A synopsis of the purpose(s) for which the linkages are required:  Death certificate/ cause of death information      Is linkage to a local dataset with <1 million patients being requested?  Yes*  No x  ** If yes, please provide further details:* |
| 1. If you have requested linked data sets, please indicate whether the Principal Investigator or any of the collaborators listed in response to question 5 above, have access to any of the linked datasets in a patient identifiable form, or associated with a patient index.   Yes*  No x  ** If yes, please provide further details:* |
| 1. Does this protocol involve requesting any additional information from GPs?   Yes*  No x  * *Please indicate what will be required:*  Completion of questionnaires by the GP*^ψ^* Yes  No  Provision of anonymised records (e.g. hospital discharge summaries) Yes  No  Other (please describe)  *^ψ^ Any questionnaire for completion by GPs or other health care professional must be approved by ISAC before circulation for completion.* |
| 1. Does this protocol describe a purely observational study using CPRD data (this may include the review of anonymised free text)?   Yes* x No**  ** Yes: If you will be using data obtained from the CPRD Group, this study does not require separate ethics approval from an NHS Research Ethics Committee.*  *** No: You may need to seek separate ethics approval from an NHS Research Ethics Committee for this study. The ISAC will provide advice on whether this may be needed.* |
| 1. Does this study involve linking to patient *identifiable* data from other sources?   Yes  No x |
| 1. Does this study require contact with patients in order for them to complete a questionnaire?   Yes  No x  *N.B. Any questionnaire for completion by patients must be approved by ISAC before circulation for completion.* |
| 1. Does this study require contact with patients in order to collect a sample?   Yes*  No x  ** Please state what will be collected* |

| 1. Experience/expertise available   Please complete the following questions to indicate the experience/expertise available within the team of researchers actively involved in the proposed research, including analysis of data and interpretation of results |
| --- |

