**Limitations of the study design, data sources and analytic methods**

The key limitation is confounding – which we discuss and seek to address in our analysis plan above. Multiple analyses will be undertaken running the risk of “statistical multiplicity” and we will guard against over-interpretation of single statistical tests(42). The key hypothesis to be tested is whether there is evidence that buprenorphine is a safer substitution drug (in relation to mortality risk) than methadone. In addition, we will corroborate earlier analyses that hypothesised that mortality risk was elevated compared to other periods immediately after treatment cessation. Several analytic approaches will be presented in order to consider the extent of confounding and to aid interpretation of the analyses.

There are missing prescription data which may lead to misclassification of periods on and off (e.g. missing amount prescribed or daily dose in order to determine last date of prescription) – which we will subject to sensitivity analysis – including using different definitions/criteria for when a patient is on/off OST and using only the last prescription. Some patients maybe treated in specialist drug treatment clinics as well as primary care, which may introduce a potential bias if the information on other periods on OST is unrecorded. We will undertake analyses to estimate the frequency of this occurrence and how CPRD can be used to identify these periods. Periods in prison are unlikely to be recorded which also may introduce bias and confer additional risks (e.g. the period in prison will be at lower mortality risk but the period immediately following prison release is a period of high risk(43)). We can estimate the likely frequency and proportion of these events from other analyses to assess potential bias, and take these biases into account in the interpretation of our findings.

The analysis of CPRD will describe mortality risk for different periods on and off treatment for further mathematical models – which include other information – such as proportion of opiate dependent people in treatment. These also are subject to uncertainty and will be explored in sensitivity analyses.

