**Use of linked data**

We will use the ONS mortality file to define overdose and drug related mortality. Previously supplied data in 2014 provided fewer deaths than expected with only 30% of deaths in the OST sample being identified as overdose or drug related. This left analyses underpowered to detect expected effect sizes. The new linkage data, set 11 covering a greater number of practices and a longer time span, offers the potential to overcome the limitations of our current data set.

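### Deaths after GP supply lapses because the patient is already admitted or dying count as post-cessation deaths, which biases the all-cause first-4-weeks-off rate ratio upward by an unknown amount

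*Protocol*

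**What the plan says.** Under Exposures, outcomes and covariates, the Protocol bases exposure on GP records: "Intervention exposure is defined by prescribing data collected by primary care practices". Time after treatment is divided into "1st 4 weeks after treatment, and rest of time out of treatment (censored at 12 months after last prescription"). The main outcome is "All and cause specific death (in particular drug poisoning/overdose) during drug treatment or follow-up period", up to a year after the last prescription. A patient's "follow up will cease either one year after the expiry of their last prescription for OST", or at death, transfer out of the practice or the end of the study period, whichever comes first. Admission and terminal illness are not in that list.

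The same section says the GP record also holds diagnoses and hospital attendances, but no rule uses them to set on/off status. The application form names one linkage: "The number of linked datasets requested: CPRD with ONS mortality register".

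Under Limitations, the protocol says "we will corroborate earlier analyses that hypothesised that mortality risk was elevated compared to other periods immediately after treatment cessation". That aim is worded as mortality risk, not overdose risk. The section accepts that treatment outside the GP record can be missed ("Some patients maybe treated in specialist drug treatment clinics as well as primary care") and that prison time is hidden. It does not mention inpatient or terminal care.

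**The concern.** A prescription record shows when GP supply ended, not why. If supply ended because the patient was already in hospital or dying, OST may have continued elsewhere, or its end may be a result of the illness that killed the patient. In either case a death within 4 weeks is counted as following cessation. The illness then causes both the apparent stop and the death, which is reverse causation.

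The error runs one way. Each such death is added to the first-4-weeks-off count and removed from the on-treatment count that serves as the comparator. The all-cause rate ratio rises on both sides. This bears on a finding the protocol sets out to corroborate, with all-cause death as a main outcome.

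The 2015 amendment makes the all-cause endpoint look more exposed than was planned. The sample size section expected about 500 of 700 deaths (71%) to be overdose. The data first supplied came back "with only 30% of deaths in the OST sample being identified as overdose or drug related".

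**Working it through.** **The plan's own figure for this window.** The sample size section gives 3123 per group for a 4-week post-treatment risk of death of 4.6% against 3.0%. With the usual two-proportion formula, two-sided 5% and 90% power:

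n = [1.96·√(2 × 0.038 × 0.962) + 1.2816·√(0.046 × 0.954 + 0.030 × 0.970)]² / 0.016² = 2999, or 3123 with continuity correction.

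The figure reproduces. The alpha and power are inferred from the match. The point disputes no number here; it shows that the post-cessation window was powered on risk of death, not on overdose.

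**Does any rule remove the misclassification?**

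- *End of follow-up:* admission neither censors nor reclassifies time.
- *Sensitivity analyses (Limitations):* on/off definitions will be varied. Changing a window for everyone does not separate illness-driven stops from true cessation.
- *Charlson Index and other covariates:* these adjust for comorbidity but do not correct misassigned person-time.
- *Marginal structural models:* these help only where the illness is recorded before the stop.
- *Self-controlled case series:* this removes time-invariant confounding. A final illness is time-varying and itself changes exposure.

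**Illustration of size.** Inputs from the sample size section:

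- on-treatment person-years: 32,000
- on-treatment death risk: 0.69%, given for methadone and used here as 0.69 per 100 person-years for all OST
- 4-week window: 3,000 person-years (methadone) or 4,200 (3,000 + 1,200 with buprenorphine). The protocol's wording covers the first 4 weeks on or after treatment, so the post-treatment share is unclear.

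On-treatment deaths: 32,000 × 0.0069 = 220.8. Taking 70% as non-overdose (from the amendment): 220.8 × 0.70 = 154.6.

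Let m be the deaths moved from on treatment to the first 4 weeks off, and P the window's person-years:

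observed IRR = [(P × 0.0069 × true IRR + m) / P] ÷ [(220.8 − m) / 32,000]

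Example with 5% moved and P = 3,000: m = 7.7; (20.7 + 7.7)/3,000 = 0.00948; (220.8 − 7.7)/32,000 = 0.00666; ratio 1.42.

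| Share moved (assumed) | m | True 1, P = 3,000 | True 1, P = 4,200 | True 8, P = 3,000 / 4,200 |
|---|---|---|---|---|
| 2% | 3.1 | 1.17 | 1.12 | 8.27 / 8.22 |
| 5% | 7.7 | 1.42 | 1.31 | 8.68 / 8.57 |
| 10% | 15.5 | 1.88 | 1.65 | 9.41 / 9.18 |
| 20% | 30.9 | 2.90 | 2.40 | 11.04 / 10.54 |

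If only 29% of deaths are non-overdose, as the original plan implies, then 5-10% is 3.2-6.4 deaths and a true IRR of 1 is seen as 1.13-1.35.

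**The case against.** **The plan already puts overdose first, and has safeguards.** The statistical analysis section frames its period hypothesis around overdose and drug-related mortality, and the outcome definition singles out drug poisoning. The policy model concerns drug-related deaths. The commitment to vary on/off definitions is worded generally, and liver and infectious-disease deaths will be examined separately. Rules for admissions might sit in an SAP not seen here. Much of this stands: the point is confined to all-cause and non-drug death, and harm to the policy model is not shown. But the aim in Limitations is still worded as mortality risk, and none of the safeguards is directed at illness-driven stopping.

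**The frequency is unknown.** The protocol does not say how often GP supply lapses because of admission or terminal illness. This stands in full, so only the direction can be asserted.

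**Stronger readings the document does not support:**

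- *That a large part of the peak is artefact.* A reader might apply 5-10% to all non-drug deaths, 700 × 0.70 = 490, and get 25-49 deaths. That count includes deaths 5-52 weeks off treatment, which cannot enter the window this way. The on-treatment base gives 8-15, about a third as many. Nor is 4.6% the overall post-cessation risk: as worded, it belongs to patients treated for 12 months or longer.
- *That 70% of deaths were not drug related.* The amendment says 30% were identified as such. It does not say whether deaths without a linked cause are in the denominator.
- *That methadone versus buprenorphine is distorted.* This needs one drug to be given to sicker patients, which the protocol does not say.

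**Reclassifying on any nearby admission would add bias.** An admission after supply has ended may be a consequence of stopping. Removing that time would pull the cessation effect toward the null. This stands and limits the fix.

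**Conclusion.** The point holds in a narrow form. As written, the exposure and follow-up rules count deaths after an illness-driven lapse in GP supply as post-cessation deaths, and this biases the all-cause first-4-weeks-off rate ratio upward. The size cannot be derived from the document. Under an assumed 5-10% shift of on-treatment non-overdose deaths (about 8-15 of 155), a true IRR of 1 would be seen as about 1.3-1.9. This rests on the methadone rate standing for all OST, the 70% share applying on treatment, and 3,000-4,200 person-years in the window.

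The mechanism would not by itself explain the more than 8-fold peak in the Background: even a 20% shift turns a null ratio into no more than 2.9. The bias matters most for modest all-cause ratios. Overdose death is much less exposed. This is a cheap improvement to the plan, not a reason to doubt that risk rises after cessation.

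**What to change.** 1. In Limitations and in the statistical analysis section, state that the corroboration of raised risk immediately after cessation rests on drug-poisoning death, with all-cause death reported alongside as supportive.
2. Add illness-driven stopping to the sensitivity analyses in Limitations, for all-cause and non-drug death. Where the CPRD diagnosis and hospital attendance records show an admission or a terminal-care code on or before expiry of the last OST supply, put the following person-time and deaths in a separate category. Report results with and without it.
3. State that admissions first recorded after supply expiry do not trigger reclassification, because they may be consequences of stopping.

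The cost is some wording and one extra exposure category built from the GP record the protocol already describes. There are two downsides. The leading cessation contrast will have fewer events, on an endpoint for which the 2015 amendment already reports a shortfall. Admissions are also incompletely recorded in primary care and no hospital linkage is named, so the sensitivity analysis will catch only part of the problem. The report should say so.
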